### Inclusion criteria and methods for data collection

Primary outcome assessment will be undertaken among women currently working as a FSW (exchanged sex for money in the past 30 days), aged 18 or older, and living or working in the study cluster for at least 6 months. We will use RDS to recruit at each site because it is practically impossible to assemble a sampling frame of the intended target population [11, 12]. At each site, we will first conduct 2 to 3 days of geographic and social mapping, including informal discussions with trained peer educators, healthcare staff, and community informants. This work informs specific criteria for ‘seed’ women to ensure that all sub-populations within the site’s sex worker population are represented and helps determine how many of these seeds should be selected. Approximately six to eight purposefully selected women (the ‘seeds’) in each site will be interviewed and given two recruitment coupons to pass on to their sex worker peers. When the women receiving the coupons attend for the interview (‘recruits’), they are also given two coupons to give out to FSW in that location. In all 14 sites, five iterations of this process (‘waves’) will be performed during both the baseline and endline surveys. Survey data will be collected directly on electronic tablet computers, and the data uploaded to a central database at regular intervals.

### Sample collection and laboratory analysis

All women will have a finger prick blood sample (DBS) collected for the detection of HIV antibody with an AniLabsytems EIA kit (AniLabsystems Ltd, [name]). Blood samples will be air-dried onto filter papers and stored at room temperature until being transported biweekly to the Flow Cytometry Laboratory in Harare. If HIV antibody is detected, then the sample will be retested for HIV viral load using NucliSENS EasyQ HIV-1 v2.0 (bioMérieux, France), both to confirm the HIV positive status and to quantify the viral load (NucliSENS EasyQ HIV-1 v2.0 is approved by the United States Food and Drug Administration, FDA, for use on dried blood spot specimens). For those samples with a positive HIV antibody test using Anilab EIA but an undetectable viral load, a second confirmatory ELISA will be performed (Enzygnost Anti-HIV 1/2 Plus ELISA, Germany). During the baseline survey at the two trial sites, plasma samples will be collected in addition to DBS and tested in parallel using NucliSENS EasyQ HIV-1 v2.0, to permit validation of the use of DBS for viral load quantification in our hands [13]. Informed consent will be obtained from all participants prior to conducting the interview and collecting blood samples.

### Ethics and regulatory approvals

Ethical approval has been received for the trial from the following institutions: the Research Council of Zimbabwe, the Medical Research Council of Zimbabwe, University College London, London School of Hygiene and Tropical Medicine and RTI International. The trial was registered at Pan African Clinical Trials Registry (PACTR201312000722390) on 9 December 2013.

### Design features requiring special consideration in reporting and analysis

Our use of RDS to recruit participants creates several issues for analysis and reporting. We seek to apply the principles and practices of the CONSORT approach for cluster randomised trials, which maximise transparency in reporting [14]. However, some aspects of our design pose challenges in this respect. First, since no sample frame exists from which the research population has been systematically sampled, it is not possible to describe individual non-participation rates in the outcome surveys or to analyse whether these differ by study arm. This step is an important component in the reporting of trial profiles. We describe below the statistics that will be possible to report and consider the strengths and limitations of these. Second, analysing the potential for sampling bias in RDS-based samples from within-study clusters will be an important component of our analysis. Of particular importance for our trial will be to assess whether there is evidence that the operationalization of RDS has introduced systematic participant recruitment bias that differs by cluster, cluster pair, or trial arm. In the case of endline surveys, we will need to investigate whether recruitment patterns through RDS change over time because of either the previous application of RDS in the study clusters, or because of an effect of the intervention in the intervention arm. The intervention seeks to strengthen the social support and increase communication within the social networks of sex workers within each cluster. This intervention might plausibly also influence patterns of peer recruitment to the RDS-survey, and relevant statistics should be reported transparently within our analysis.

Finally, we must select a primary analysis approach suitable for the structure of our data. As described below, since we are conducting a cluster randomised trial with a relatively small number of clusters, we will use a cluster-summaries approach. Our primary analysis will be based on the two-stage approach of Hayes and Moulton [15] adapted for use with RDS. We will consider an unadjusted analysis as a sensitivity analysis. We describe our preferred approach in the next section, and consider the strengths and limitations in relation to alternatives in the discussion.

### Statistical analysis plan

#### Analysis principles

We hypothesise that after 2 years, a lower proportion of FSW from the study clusters, which have been randomised to receive the combination SAPPH-IRe intervention, will have an HIV viral load ≥ 1000 copies/ml than FSW from comparison clusters. Our analysis will be based on an intention-to-treat principle in that the primary analysis will compare FSW recruited in RDS surveys in each community without considering direct contact with the intervention components. Analysis will be appropriate for the matched-cluster-pairs design of the study. Data from individual FSW will be summarised for each cluster as described below, and we will express the intervention effect in the form of a prevalence ratio and show associated 95 % confidence intervals. We will interpret there to be strong evidence against the null hypothesis of no intervention effect if the 95 % confidence interval of the prevalence ratio excludes 1.

Our estimation of cluster summaries will need to take account of the RDS methodology used to recruit participants. A range of literature describes approaches to handling data from RDS surveys. Our approach will be based on the RDS-2 methodology developed by Volz and Heckathorn [16], which has been found to be less biased than the earlier Salganik-Heckathorn estimator [9, 17–19]. RDS-2 conceptualises RDS recruitment as a random walk sampling process throughout the entire social network of FSW at each site. Under this assumption, the probability of recruitment of any one non-seed FSW to the research sample is proportional to their number of FSW social contacts, or ‘degree’ in network terminology [16]. Consequently, FSW with a higher ‘degree’ have a greater probability of appearing in the final research sample than those with a lower degree. In generating cluster-summaries, we will therefore conduct a weighted-analysis in which individuals are weighted with proportion to 1/self-reported out-degree. The question we will use to estimate network degree is ‘the number of sex workers a participant reported knowing who were at least 18 years old, lived at the site, and who the participant would consider recruiting to the study’.

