## Methods/Design

### Design

The trial is a matched, cluster randomised controlled trial, Fig. 1. Trial sites have been purposively selected to be reflective of a range of settings, they are of adequate size to ensure participation of between 85 and 300 new FSW annually, and they are located at geographic spacing sufficient to ensure that the risk of contamination/spill-over of intervention effect between study clusters through FSW mobility and migration is minimised. A cluster was defined as the FSW population working in the geographic location around a government health clinic where dedicated FSW services are being delivered.

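### The degree question behind every RDS-2 weight counts only contacts who live at the site, whereas women who only work there are also eligible and recruitable

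*Protocol article*

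**What the plan says.** Under *Analysis principles*, the protocol article treats recruitment as a "random walk sampling process throughout the entire social network of FSW at each site". It draws from this that "the probability of recruitment of any one non-seed FSW to the research sample is proportional to their number of FSW social contacts", and so "individuals are weighted with proportion to 1/self-reported out-degree". The same paragraph gives the degree question as the number of sex workers known who were aged 18 or older, "lived at the site, and who the participant would consider recruiting to the study".

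Two other places describe the population over which coupons travel. *Inclusion criteria and methods for data collection* admits women "living or working in the study cluster for at least 6 months", and has participants pass coupons to sex workers at the location with no residence condition. *Design* states: "A cluster was defined as the FSW population working in the geographic location around a government health clinic".

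**The concern.** The RDS-2 weight corrects for unequal recruitment probability only if the degree counts the ties along which a woman could be recruited. Here the weight counts ties to residents, while recruitment also runs along ties to women who work at the site and live elsewhere. A woman whose contacts are largely work-only reports too small a degree and receives too large a weight.

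This degree enters every cluster summary in the primary analysis, at baseline and at endline. No planned check is described that would show the problem. The second degree report at the incentive visit tests repeatability, and a definition that is too narrow can be perfectly repeatable. The sensitivity analyses drop the weights, take the higher of the two degree reports, or use the successive-sampling estimator. None describes a degree that includes work-only contacts.

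**Working it through.** The article gives no figure for this point, so there is nothing to reproduce. The check has three parts.

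**1. The place criterion, side by side**

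| Element | Place criterion |
|---|---|
| Cluster definition (*Design*) | works there |
| Survey eligibility (*Inclusion criteria*) | lives or works there |
| Coupon recipients (*Inclusion criteria*) | at the location, no residence limit |
| Degree question (*Analysis principles*) | lives there |

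The clause on whom the participant would consider recruiting does not close the gap. It is joined to the residence condition by 'and', so it can only narrow the count further.

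**2. Bias in one cluster summary (illustration; all inputs assumed)**

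Take residents R and work-only women W, where W is a share q of the eligible population. True degree is equal in the two groups, ties are reciprocal, and homophily is h (the share of ties forced within group).

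- Resident share of contacts: aR = h + (1 − h)(1 − q) for R, and aW = (1 − h)(1 − q) for W.
- Weighted share of W when the weight is 1/(resident contacts): s = (q/aW) / [q/aW + (1 − q)/aR]. The correct share is q.
- Bias = (s − q) × (prevalence in W − prevalence in R).

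Example, q = 0.20 and h = 0.5: aR = 0.90 and aW = 0.40, so s = 0.500/(0.500 + 0.889) = 0.36. With a 10-point gap the bias is (0.36 − 0.20) × 10 = 1.6 points.

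| q | h | aR | aW | s | Bias, gap −10 | Bias, gap +10 | Bias, gap +20 |
|---|---|---|---|---|---|---|---|
| any | 0 | 1 − q | 1 − q | q | 0 | 0 | 0 |
| 10 % | 0.25 | 0.925 | 0.675 | 13.2 % | −0.3 | +0.3 | +0.6 |
| 10 % | 0.5 | 0.95 | 0.45 | 19.0 % | −0.9 | +0.9 | +1.8 |
| 20 % | 0.25 | 0.85 | 0.60 | 26.2 % | −0.6 | +0.6 | +1.2 |
| 20 % | 0.5 | 0.90 | 0.40 | 36.0 % | −1.6 | +1.6 | +3.2 |
| 30 % | 0.25 | 0.775 | 0.525 | 38.7 % | −0.9 | +0.9 | +1.75 |
| 30 % | 0.5 | 0.85 | 0.35 | 51.0 % | −2.1 | +2.1 | +4.2 |

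Biases are in percentage points. If the question counted women who live or work at the site, s would equal q and the bias in this model would be zero in every row.

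**3. Consequence for the prevalence ratio**

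The planning values in the notes to Fig. 2 are 41 % and 28 %, a ratio of 28/41 = 0.683.

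- Same bias in both arms: +1.6 points gives 29.6/42.6 = 0.695. The extremes of the table give 32.2/45.2 = 0.712 (+4.2) and 25.9/38.9 = 0.666 (−2.1).
- Bias in the intervention arm only, +1.6 points: 29.6/41 = 0.722.
- Effect differing by residence (assumed: 41 % for all comparison women; in the intervention arm 28 % for residents and 41 % for work-only women, q = 20 %). The true value is (0.8 × 28 + 0.2 × 41)/41 = 30.6/41 = 0.746. With s = 36 % it becomes (0.64 × 28 + 0.36 × 41)/41 = 32.7/41 = 0.797.

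**The case against.** The strongest reply is that a mismatch in wording is not in itself a bias. The weights are normalised within the cluster, so undercounting every woman's degree by the same fraction changes nothing. A biased summary needs three things together: a material work-only share, mixing by residence, and a different outcome prevalence in that group. The documents give a figure for none of them. This stands, and it limits what can be claimed.

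A reader might infer that mobile women are over-weighted and site prevalence is therefore overstated. The documents do not support this. Nothing links residence to mobility or to viral load, the six-month rule removes recent arrivals, and the sign reverses if work-only women have lower prevalence.

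A reader might also infer that the trial effect is biased. The wording is the same in all sites, and a bias common to both arms hardly moves the ratio. A larger shift needs a difference by arm or by residence. The discussion section regards intervention-driven network change as plausible, but nothing shows that it changes mixing by residence.

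The degree question also omits the 30-day and six-month criteria. That is not part of this point. The clause on women she would consider recruiting partly screens for eligibility. A participant often cannot know when a contact last sold sex or how long she has been at the site, and *RDS diagnostics* itself warns that RDS-2 is sensitive to errors in reported degree.

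The unweighted sensitivity analysis does not depend on the degree question, and agreement with it would be reassuring. It also removes the correction that the weights are there to make, so disagreement could not be traced to residence. Finally, the questionnaire may word residence differently from the article. However, the article presents this wording as the question to be used, and the sponsor can check it against the instrument.

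**Conclusion.** The point holds as a stated measurement rule that departs from the requirement the article itself sets for RDS-2. The degree is restricted to residents, while eligibility, coupon flow and the cluster definition all take in women who only work at the site. Nothing in the article reconciles these.

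The size and direction of any bias cannot be established from the documents. It is zero if the resident share of contacts is constant across women. It is about −2 to +4 points per site at homophily 0.5 under the assumed shares and gaps, and smaller at homophily 0.25. The planned ratio of 0.683 shifts by no more than about 0.03 when that bias is common to both arms. Larger shifts (about 0.04 to 0.05 in the examples) need a difference by arm or by residence, which is assumed here and not shown. The point merits action because it is cheap to correct before endline and cannot be repaired afterwards.

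**What to change.** At the April/May 2016 endline, ask the degree question with its place criterion matched to eligibility: sex workers known, aged 18 or older, who live or work at the site, and whom the participant would consider recruiting. Repeat it at the incentive visit so that the test-retest check and the higher-of-two-reports analysis apply to the new item. Do not add the 30-day or six-month criteria.

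Keep the baseline wording as a second item, so that the planned baseline-to-endline comparison of degree remains like with like. Pre-specify the live-or-work answer for the endline RDS-2 weights, and report the effect with weights from the old wording as a sensitivity analysis.

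The cost is one or two extra survey items. Baseline is complete and stays on the old definition, so endline summaries would be adjusted for baseline summaries weighted slightly differently. That is tolerable because baseline enters only as a cluster-level covariate.

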### Study profile

We will describe the number of clusters recruited to each arm of the study at baseline and document the drop-out of any full study clusters during the trial period. Cluster drop-out is not expected but might occur if political or community acceptance for the research protocol is compromised during the trial duration.

For each arm of the study, we will describe, at both baseline and at the end of the follow-up, the range and mean size of the sample recruited through the RDS surveys in each site. We will produce participant recruitment trees to describe the RDS recruitment process in every cluster. Because it is participants who approach other new potential participants, it is not possible for us to directly measure the refusal rate. We will describe by arm and at baseline and endline, the range and cluster-mean of the number of women who do not forward recruit two participants. At endline, we will ask women how many FSW they tried but failed to recruit and their understanding of the reasons for their refusal. For each arm, the range and mean of participants in each cluster with missing data for the primary outcome will also be documented. These data will be used to construct a trial profile diagram in line with CONSORT principles, but adapted for our specific situation.

### RDS diagnostics

The random walk model upon which RDS-2 estimation is based makes a number of assumptions about the sampling process. These include that participants are able to accurately report their network size and that they recruit randomly from within this network; that seed characteristics do not bias the final estimates; that the whole social network of female sex workers is connected at each site; and that social ties are reciprocated (recruitees also know their recruiters). The model also assumes with-replacement sampling – that is, that participants can be recruited more than once, which is not the case in practice. However, the extent to which some of these assumptions might be biasing study findings can be tested using information collected in the survey and from a brief follow-up interview when participants return to collect their incentives for recruiting others. We will conduct a set of recommended RDS diagnostics for each site, as recommended by Gile et al. [20], to assess the extent to which the actual sampling process differed from the model. We will report our findings according to emerging STROBE guidelines for the reporting of RDS surveys [21].

RDS studies have typically assessed the possible impact of biases on an estimated proportion through simulation of a social network and/or of the RDS process that runs over it [17, 22, 23], through there are a few examples where biases could be empirically tested [9, 24]. For our study, we are primarily interested in assessing whether deviation from the assumed recruitment process might be differential by intervention arm and thus differentially biasing site estimates and study findings. We therefore investigate assumptions as follows, by study arm.

First, for each site and categorised by arm, we will examine graphically the extent to which the cumulative estimates for our primary and secondary outcomes stabilise from the initial seed characteristics over successive waves of recruitment [20]. The random walk model requires the assumption that the final estimates are no longer influenced by initial seed characteristics. Secondly, we will use the same graphical method to assess whether the estimates for each seed converge. If seed-specific estimates remain different from each other by the final sample wave, this observation might suggest that the population is split or extremely clustered into separate sub-groups rather than fully connected as the random walk model assumes [20].

We will also assess whether deviation from random recruitment varies by arm [25]. When we ask participants to estimate their network size, we will also ask them to describe the characteristics of these FSW, including the proportion who are under 25 years, who engage in different types of sex work and other characteristics to judge whether recruitment from among each woman’s pool of potential recruitees is related to any of these factors. We will also ask participants to describe their relationship to their recruiter and recruitees to confirm reciprocity (that both women did know each other previously as the model assumes). This will enable us to assess the random recruitment assumption by comparing the recruiter-recruitee characteristics to other women in the group of potential recruitees [26].

RDS-2 estimates have been found to be sensitive to errors in reported degree, particularly in participants with low degrees whose status has a higher weight [27]. When participants return to collect incentives, we will ask them to estimate the size of their network a second time, and we will calculate test-retest reliability of this estimate. RDS also assumes that all social contacts are reciprocated, so we will investigate the extent to which this is true and the extent to which recruitment might vary by relationship characteristics [28] by asking participants about their relationship with their recruiter.

If the community mobilisation and adherence support activities change the structure and composition of the FSW social networks in the intervention sites, possibly, the RDS sampling process that runs over these networks might be differentially biased by the trial arm. RDS surveys have been used to characterise the underlying social network [22, 29]. To investigate whether unobservable biases might have occurred, we will examine the measures that describe the character of the FSW social network at each site by: 1) comparing changes in mean and median degree reported at baseline and at follow-up in intervention versus usual care sites; 2) comparing the levels of homophily (similarity) between FSW and their personal networks, and between recruiters/recruitees; 3) comparing changes in reported social cohesion and the proportion of sex workers reporting good relations with other sex workers; and 4) examining whether the conditions of recruitment (place of recruitment, relationship between recruiter/recruitee, and motivation for recruitment) differ between arms.

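### The degree comparison meant to detect intervention-driven network change names no 1/degree weighting; taken at face value it can understate a change, or reverse its sign when new ties form mainly among poorly connected women

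*Protocol article*

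**What the plan says.** Under RDS diagnostics, the protocol article recognises that community mobilisation may change the sex workers' networks and so bias recruitment differently by arm. To investigate this, it states that "we will examine the measures that describe the character of the FSW social network at each site", and lists four measures. The first is "comparing changes in mean and median degree reported at baseline and at follow-up in intervention versus usual care sites". The other three cover homophily, reported cohesion and good relations, and the conditions of recruitment.

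Under Analysis principles, the sampling model is that "the probability of recruitment of any one non-seed FSW to the research sample is proportional to their number of FSW social contacts". The remedy follows: "In generating cluster-summaries, we will therefore conduct a weighted-analysis in which individuals are weighted with proportion to 1/self-reported out-degree".

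The section on design features requiring special consideration explains why network change is expected: "The intervention seeks to strengthen the social support and increase communication within the social networks of sex workers within each cluster".

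**The concern.** The aim of the first measure is the network at each site. The statistic named is a mean and a median of the degrees that recruited women report. By the article's own model, those women are not a representative sample of the network with respect to degree, because well-connected women are over-represented in proportion to the very quantity being summarised. The weighting that corrects this is tied to cluster summaries. That term is used for participant characteristics and for the primary outcome, but not for this measure.

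The Discussion treats arm-differential bias from altered networks as potentially the most serious threat to the trial. The listed sensitivity analyses (no RDS-2 weighting, the higher of two reported degrees, the successive-sampling estimator) do not directly test for such a change. Much of the evidence on it will therefore come from these descriptive measures, and degree is the one linked directly to the RDS-2 weights.

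**Working it through.** The article reports no degree figure, so there is nothing to reproduce. All degree values below are assumptions. Inputs from the article are recruitment proportional to degree (Analysis principles), reciprocated ties (RDS diagnostics) and about 200 women per site (Sample size calculations).

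**Formulas.** Let d be degree in the network. With inclusion proportional to d:

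- the plain sample mean estimates E[d²]/E[d] = mean + variance/mean;
- the 1/degree-weighted mean, n/Σ(1/d), estimates E[d].

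The plain mean therefore responds to the spread as well as the mean, and narrowing the spread pulls it down.

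**Two-point example.** Half the women have 2 contacts and half have 18. The first half then rises to 10.

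- True mean: (2+18)/2 = 10, then (10+18)/2 = 14, a rise of 40%.
- Expected plain mean: (4+324)/20 = 16.4, then (100+324)/28 = 15.1.
- Variance form: 10 + 64/10 = 16.4, then 14 + 16/14 = 15.1.
- Plain median: 18 both times, since 18/20 = 90% and then 18/28 = 64% of recruits come from the upper group.
- Weighted mean: 1/(0.10/2 + 0.90/18) = 10, then 1/(0.357/10 + 0.643/18) = 14.

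**Median, three-point example.** Of the women, 50% have 2 contacts, 15% have 8 and 35% have 20. The first group then rises to 8. The network median goes from 2 to 8, while the plain sample median stays at 20 because 7/9.2 = 76% and then 7/12.2 = 57% of recruits have 20 contacts. The true mean goes from 9.2 to 12.2 and the plain mean from 16.5 to 14.9.

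**How far the reversal extends.** Take degrees 2 and 20, with a low-degree share of 20% to 60%. The plain mean falls in every case when the low group rises to 5, 8 or 12, and rises slightly when it reaches 18. At a 50% share:

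| Low group rises to | True mean, from 11.0 | Plain mean, from 18.4 |
|---|---|---|
| 5 | 12.5 | 17.0 |
| 8 | 14.0 | 16.6 |
| 12 | 16.0 | 17.0 |
| 18 | 19.0 | 19.1 |

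**Reciprocated ties.** In the examples above the well-connected group gains nothing. With reciprocated ties, this requires every new tie to lie within the low-degree group. A simulated network relaxes that: 1000 women, half with expected degree 2 and half with 20, and 500 degree-proportional samples of 200 drawn without replacement. At baseline the true mean is 11.0, plain mean 18.8, plain median 20.0 and weighted mean 11.0.

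| New ties of low-degree women go to | True mean | Plain mean | Plain median | Weighted mean |
|---|---|---|---|---|
| other low-degree women | 14.0 | 17.1 | 18.3 | 13.6 |
| high-degree women | 17.0 | 21.9 | 24.4 | 16.4 |
| random women | 17.0 | 19.6 | 20.5 | 16.7 |

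With random ties, a true rise of 6.0/11.0 = 55% shows as 0.8/18.8 = 4% in the plain mean. The weighted mean is not exact here, because sampling is without replacement and 7.1% of the simulated women had no contacts at baseline.

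**Every woman gains 5 contacts** (2 and 20 become 7 and 25). The true mean goes from 11.0 to 16.0 (45%) and the plain mean from 18.4 to 21.1 (15%). The direction is right but the size is understated.

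**Where weighting does not help.** Suppose 30% of women have no contacts, 35% have 10 and 35% have 20, and the first group rises to 4. The true mean rises from 10.5 to 11.7. The plain mean falls from 175/10.5 = 16.7 to 179.8/11.7 = 15.4. The weighted mean falls further, from 10.5/0.7 = 15.0 to 11.7, because women with no contacts could not be recruited at baseline.

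**Sensitivity to low reports.** Take 200 recruits from the first example at baseline, 20 with degree 2 and 180 with 18. The weighted mean is 200/(20/2 + 180/18) = 10. If 5 of the 20 report 1 instead of 2, it becomes 200/(15/2 + 5/1 + 180/18) = 200/22.5 = 8.9. The plain mean barely moves: 3280/200 = 16.40 to 3275/200 = 16.38.

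**The case against.** The article never says that the comparison is unweighted. Elsewhere it uses the word reported to mean self-reported, so the word alone does not imply an unweighted summary. A site-level mean degree could be read as a cluster summary, which would carry the weights, and an article may leave such detail to a full plan. This stands as far as it goes: a reader might infer that the plan prescribes an unweighted analysis, and the text does not establish that. What remains is that the weights are stated for cluster summaries and this item does not invoke them, so an analyst following the words could properly compute the plain mean and median.

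A reader might also infer that the trial would conclude that mobilisation left the networks unchanged. The article does not support this. It sets no threshold or decision rule and fixes no direction. A move from 16.4 to 15.1 would still be shown as a change, and degree is one of four measures, supported by the convergence, reciprocity, random-recruitment and test-retest checks.

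The wrong sign is conditional. In the simulation, the plain mean rose when new ties went to well-connected or random women. The fixed median in the simple examples partly reflects their few degree values; in the simulation it did move. Finally, weighting is not a complete cure: it does worse than the plain mean when previously unconnected women enter the network, and it is sensitive to low reported degrees, an error that RDS diagnostics itself warns about. These points limit the concern but do not remove it.

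**Conclusion.** The point holds as a cheap improvement to a descriptive diagnostic. Under the article's own sampling model, a plain mean of reported degree is not a measure of the network's mean degree. It can understate a network change, and can move the wrong way when new ties form mainly among poorly connected women. In the assumed scenarios the distortion ranges from a rise of 45% seen as 15%, through 55% seen as 4%, to a rise of 40% seen as a fall of 1.3/16.4 = 8%. No size can be given for this trial without its degree distribution.

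A reader might infer that the trial's effect estimate is affected. It is not: this comparison does not enter it. The conclusion rests on recruitment proportional to degree and on reasonably accurate self-reported degree. It does not extend to women with no contacts, for whom neither version is reliable.

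**What to change.** In the first of the four network measures under RDS diagnostics, state that the RDS-2 weighted mean degree, n/Σ(1/degree), and the weighted median will be reported by site, survey and arm beside the raw mean and median, and that network change will be interpreted from the weighted values.

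Add two limits. The weighted values are sensitive to errors in low reported degrees, which the planned second report of network size can help to gauge. Women with no contacts cannot be sampled, so neither version is reliable if such women join the network during the trial.

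Applying the same weights to the third measure (cohesion and good relations) is optional, since it presumes that those answers vary with degree.

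The cost is a few sentences in the plan. The weights are already needed for the primary analysis and no new data are required.
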